### 5.3. STUDY

#### 5.3.1. Inclusion

The inclusion and non-inclusion criteria will be checked during a medical consultation with the patient. This consultation will be carried out as soon as the patient arrives in the department or, at the latest, before the completion of late acquisitions (approximately 2 hours after the injection ).

Information and consent will be obtained during this consultation with one of the doctors on duty. During this consultation, the various criteria for inclusion and non-inclusion will also be checked.

After a decision period, if patient participate in this study, the various documents will be collected in the patient's file, at the latest before the late pictures of the standard scintigraphy examination are taken.

At any time, the patient may, if patient indicates his refusal, leave the study. In this case, only acquisitions necessary for the standard examination will be made.

#### 5.3.2. Patient follow-up

No patient follow-up, other than that required for the pathology explored in standard scintigraphy, will be required for the study.

## 5.4. RESEARCH DURATION

The inclusion period will take place over a period of 12 months after the CPP has given its approval for the study to be carried out and the equipment to be made available (collimator...).

The total duration of the patient's participation will not exceed half a day.

## 5.5. MEASURES TAKEN TO REDUCE AND AVOID BIAS

### EXAMEN STANDARD

[figure not shown]

### EXAMEN DE RECHERCHE

[figure not shown]

### 5.5.1. Drawing of lots

A draw will not be carried out because the standard examination will always be carried out first in order not to cause a loss of chance if the examination is stopped (patient with pain...). This also allows the patient to refuse to participate in the study at the end of his or her standard examination. The protocol will be adapted to compensate for the delay between the two examinations (increased acquisition time in proportion to the radioactive decrease).

Patients will be included consecutively. Images will be realized first on the GE camera, equipped with the LEHRS collimator, or on the Siemens camera, with LEHR collimator, depending on his initial appointment slot. However, when 50% of the study population has been achieved on one of the two cameras, the inclusions will only continue on the other.

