| MAIN OBJECTIVE              | Compare image quality obtained with the new LEHRS GE collimator versus a standard Siemens LEHR collimator in bone scan studies.                                                                                                                                                                                                                                                                                                                                                              |
| SECONDARY OBJECTIVES        | Evaluation of image quality in pulmonary, thyroid, parathyroid and brain scans with DaTSCAN.

Performances evaluation on physical measurement phantoms.                                                                                                                                                                                                                                                                                                                                |
| MAIN JUDGMENT CRITERION     | Rate of images obtaining a score greater than or equal to 4 on visual image quality analysis (on a 5-point LIKERT scale).                                                                                                                                                                                                                                                                                                                                                                    |
| SECONDARY JUDGMENT CRITERIA | Signal-to-noise ratio measurements on patient acquisitions.

Physical performances of the new LEHRS collimator using physical measurement phantoms.                                                                                                                                                                                                                                                                                                                                    |

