## **2.2. DESCRIPTION OF THE STRATEGY STUDIED**

Exam protocol will be conforme to French and international medical societies recommandations. According to indication, early images will be realized after radiopharmaceutical drug injection. Late bone scan images will systematically be realized 2 hours after injection (for the radiopharmaceutical drug used in our department), mentioned as whole-body scan. This acquisition is often complemented by additional planar acquisitions, focused on a region of interest (most often the painful area and/or pathologic bone uptake).

In some cases, a tomoscintigraphy will be performed, allowing to obtain 3D volume scintigraphy images, improving the sensitivity of detection of small abnormal bone fixations. This acquisition of tomoscintigraphy will be associated with CT scans for more accurate anatomical localization.

In addition to this standard examination, the patient's participation in the research protocol will involve the creation of complementary images with the new collimator : a second whole body

[figure not shown]

scan, a static acquisition, and in cases where it has been requested for the standard examination, a tomoscintigraphy (without CT in this case, to maintain dosimetry equivalent to the standard examination).

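### Sections 2.2 and 5.5.1 conflict on which collimator is scanned first, and the 50% cap on order covers all 85 patients instead of the 70 bone-scan patients

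*Protocol*

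**What the plan says.** Three statements in the protocol bear on acquisition order.

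- Section 5.5.1, first paragraph: "A draw will not be carried out because the standard examination will always be carried out first". The reason given is to avoid a loss of chance if the session is cut short, and to let the patient decline the study once the standard scan is done.
- Section 2.2: participation "will involve the creation of complementary images with the new collimator : a second whole body" scan, plus a static view and, where requested clinically, a tomoscintigraphy without CT. The Executive Summary attaches the word standard to the Siemens device: "Compare image quality obtained with the new LEHRS GE collimator versus a standard Siemens LEHR collimator in bone scan studies".
- Section 5.5.1, second paragraph: "Images will be realized first on the GE camera, equipped with the LEHRS collimator, or on the Siemens camera, with LEHR collimator". Which of the two applies to a given patient is settled by the booking: "depending on his initial appointment slot". A balancing rule follows: "when 50% of the study population has been achieved on one of the two cameras, the inclusions will only continue on the other".

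The delay between scans is compensated by "increased acquisition time in proportion to the radioactive decrease". The Executive Summary plans 85 patients, 70 of them for bone scans, and the main objective concerns bone scans only. Section 5.6 records acquisition times.

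**The concern.** Each patient is scanned twice after a single injection, so one collimator always works on the later image. Lengthening the acquisition restores counts lost to decay. It does not act on other things that may change between the scans, such as tracer distribution, movement or fatigue. The Likert scale in Section 3.3 grades bone fixation, background noise and sharpness, so such changes could reach the primary score.

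The two order rules have different consequences. Under one, LEHRS is second in every patient and no analysis can separate collimator from order. Under the other, about half the patients have each order and most of an order effect cancels. A reader of the protocol cannot tell which applies. In a non-inferiority comparison, an advantage to the second scan would favour LEHRS under the fixed order, and a disadvantage would count against it.

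**Working it through.** **Step 1: the passages side by side.** If the standard examination in Section 5.5.1 means the Siemens LEHR scan, as the Executive Summary's wording and Section 2.2 suggest, the first paragraph puts LEHRS second in everyone. The second paragraph contradicts this. If it means the clinical scan on whichever camera was booked, the two paragraphs of Section 5.5.1 agree, but Section 2.2 does not fit. It makes the new-collimator images the added ones for every patient. No single reading fits all three statements.

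**Step 2: how an order effect enters.** Let τ be the true LEHRS minus LEHR difference in the rate of scores 4 or 5, and π the second-minus-first order effect. The expected paired difference is τ + π for Siemens-first patients and τ − π for GE-first patients. Pooled over n patients:

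bias = π × (n Siemens-first − n GE-first) / n

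**Step 3: fixed order.** All 70 bone patients are Siemens-first, so bias = π × 70/70 = 100% of π.

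**Step 4: slot rule with the cap on 85.** Non-bone patients number 85 − 70 = 15. Half of 85 is 42.5, so the cap is 42 or 43.
- Cap 43: at worst 43 bone patients start on one camera. The other has 27 bone plus 15 non-bone patients, 42 in all. The weight is (43 − 27)/70 = 23%.
- Cap 42: the worst bone split is 42/28, weight 14/70 = 20%.
- If slots are unrelated to indication, the number of bone patients on a given order is hypergeometric (85 patients, 42 or 43 on that order, 70 bone). The mean absolute weight is 4.0%, and the chance of 40/30 or worse is 1.1%.
- Cap within bone scans: 35/35, weight 0.

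**Step 5: translation into points.** π is an assumption, as the documents give none.

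| Assumed π | LEHRS always second | 43/27 | 35/35 |
|---|---|---|---|
| 2 points | 2.0 | 0.46 | 0 |
| 5 points | 5.0 | 1.14 | 0 |
| 10 points | 10.0 | 2.29 | 0 |

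**Step 6: illustration for the non-inferiority test.** The protocol states no margin or discordance, so both are assumed. With weight w, margin M, discordance q and true difference −M, put d = −M + πw and SE = √((q − d²)/70). The chance of wrongly declaring non-inferiority is Φ((d + M)/SE − 1.96). Take M = 10 points, q = 20% and π = 5 points favouring the second scan:
- w = 1: d = −0.05, SE = 0.0531, result 15.4%
- w = 16/70: d = −0.0886, SE = 0.0524, result 4.1%
- w = 0: result 2.5%

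With M kept at 10 points, q from 15% to 30% and π from 2 to 10 points, the range is 4.9% to 57.9% for the fixed order and 2.9% to 7.3% at 43/27.

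**Step 7: cost of adjusting.** The unweighted mean of the two order-specific differences has expectation ((τ + π) + (τ − π))/2 = τ. With equal within-stratum variance, its variance relative to a balanced split is 0.25 × (1/43 + 1/27) × 70 = 1.055 at 43/27. The effective n is 70/1.055, about 66.

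**The case against.** The strongest reply is that no sentence says outright that LEHRS is always second. That follows only if the standard examination is equated with the Siemens collimator. The cap and switch in Section 5.5.1 would have no purpose under a fixed order, and the loss-of-chance reason requires only that the clinically needed scan be finished first, on whichever camera was booked. Sections 4.4 and 5.2 mention a second scan or two collimators without naming an order. The diagrams under Section 5.5 are not shown and may settle the sequence. This stands: a reader might infer that the design is fully confounded, but the documents do not establish it. What remains is that Section 2.2 says otherwise and the term is undefined.

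A reader might also infer that the analysis wrongly ignores order, because Section 8 names no order term. That is not supported as an error. Such a term is commonly left to the statistical analysis plan, which is not shown, and the recorded acquisition times allow for it.

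Finally, the 43/27 split is an extreme. At the expected weight of about 4%, an assumed 5-point order effect gives about 0.2 points of bias, so the choice of population for the cap is a small matter in itself.

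**Conclusion.** The conflict between Section 2.2 and Section 5.5.1 is real and must be reconciled before the primary comparison can be interpreted. Its consequence depends on the answer. With LEHRS always second, 100% of any order effect that survives the decay compensation is inseparable from the collimator. With both orders, order is set by a non-random slot, and closing one camera at 50% also ties it to calendar time. At most 23% of an order effect then enters the unadjusted difference, and about 4% in expectation if slots are unrelated to indication.

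These percentages follow from the planned 85 and 70 and an additive order effect. The bias in points and the false non-inferiority rates rest on assumed order effects, margin and discordance. The documents do not show that an order effect exists, so it would be wrong to read these figures as a demonstrated bias.

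**What to change.** State one order rule in Sections 2.2 and 5.5.1, and define the standard examination so that it means the same thing in both. Which rule to adopt is for the sponsor, since the protocol gives a patient-protection reason for its order.

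- **If both orders are used:** apply the 50% cap within bone-scan patients (35/35). Estimate the primary difference as the unweighted mean of the GE-first and Siemens-first paired differences, with order-stratified variance, taking order from the acquisition times already recorded. This removes an additive order effect, provided that effect and the collimator effect are alike in the two groups.
- **If LEHRS is always second:** delete the either-camera paragraph and its cap, and state that collimator and order cannot be separated.

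Random allocation of the first camera at booking is not requested. Sections 4.3 and 5.3.1 obtain consent only after arrival, so it would redirect the clinical scans of people who have not yet agreed to take part.

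The cost is protocol wording, slightly less scheduling freedom, and about 5.5% more variance if the bone split still ended at 43/27 (none at 35/35).

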### **3.4. SECONDARY EVALUATION CRITERIA**

The secondary evaluation criteria will be:

- Physical measurements of collimator performances on phantoms.
- Evaluation of the signal-to-noise ratio in bone scan images (sacroiliac fixation ratios / soft tissue on whole body scanning) obtained using the two sets of collimators.
- A quantified assessment (Likert scale) of the image quality obtained in lung, thyroid, parathyroid or brain scintigraphic examinations at DaTSCAN.
- An evaluation of the signal-to-noise ratio in brain scan images at DaTSCAN, by comparing the striata/occiput fixation ratios obtained using the two sets of collimators, after automatic analysis and segmentation in DaTQUANT (GE) software.

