#### **4.4. BENEFIT / RISK**

Participation to this study does not create any additional risk for the patient, since the completion of the 2nd scintigraphy does not change the posology, mode and frequency (single injection) of the injected radiopharmaceutical drug.

The patient will maybe benefit from image quality improvement and an exam review by 2 expert physicians. The only constraint for the patient will be an extended examination time of 15 to 30 minutes, compared to a "standard" examination, without any further invasive procedures or additional irradiation.

Collectively, image quality improvement with this collimator could reduce the duration of exams and/or the posology of radiopharmaceutical drugs (improvement of patient dosimetry).

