## **5.6. DATA COLLECTED IN THE OBSERVATION BOOKLET**

- Patient data: age, sex, weight, BMI.
- Radiopharmaceutical drug-related data: radiopharmaceutical drug name, injected activity, time and injection site.
- Data related to acquisitions: acquisition times, physical parameters (peak energy, fenestration, acquisition time, time per projection and number of projections if tomoscintigraphy...)

As with the standard review, the study imaging data will be stored and archived in the institution's PACS.

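### Lengthening the second acquisition for decay restores counts but cancels from the sacroiliac/soft-tissue ratio, so any effect of time since injection stays in the paired difference

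*Protocol*

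**What the plan says.** Protocol section 5.5 sets out the measures against bias. Under 5.5.1 the delay between the scans is handled by one rule: "The protocol will be adapted to compensate for the delay between the two examinations (increased acquisition time in proportion to the radioactive decrease".

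Section 5.2 has both scans use the activity already injected for the standard examination, so they fall at different times after one injection. Section 2.2 fixes the time of the standard images ("Late bone scan images will systematically be realized 2 hours after injection") and the visible text gives no time for the second scan. The only figure near the delay is in section 4.4: "an extended examination time of 15 to 30 minutes".

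The endpoint concerned is secondary, in section 3.4: "Evaluation of the signal-to-noise ratio in bone scan images (sacroiliac fixation ratios / soft tissue on whole body scanning) obtained using the two sets of collimators". The same section lists a DaTSCAN counterpart, "by comparing the striata/occiput fixation ratios obtained using the two sets of collimators".

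On order, 5.5.1 first says the standard examination always comes first. It then lets either camera be first according to the appointment slot, with inclusions closing on a camera once it holds 50% of the study population. Section 2.2 says "participation in the research protocol will involve the creation of complementary images with the new collimator" and describes a second whole-body scan.

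Section 8 names a Wilcoxon signed rank test for categorical and non-Gaussian variables, with no term for time or order. Section 5.6 records the injection time and "Data related to acquisitions: acquisition times, physical parameters (peak energy, fenestration, acquisition time, time per projection and number of projections if tomoscintigraphy".

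**The concern.** The rule is offered as compensation for the delay. It does compensate for what physical decay takes away, namely counts. An uptake ratio taken within one image is different: decay and acquisition time act equally on numerator and denominator, so the rule leaves its expected value unchanged. If soft tissue and bone handle the tracer differently between the scans, the ratio moves for a reason unrelated to the collimator.

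The consequence depends on scan order. With both orders present in similar numbers, the movement is positive in some pairs and negative in others, so it mostly widens the spread of the differences. With one fixed order it is inseparable from the collimator. If the new collimator were always second and soft tissue cleared while bone held its tracer, the drift would favour the new device.

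**Working it through.** The plan states no figure for this effect, so there is none to reproduce.

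**Inputs from the protocol:** one injection (5.2); 85 patients, 70 of them bone (executive summary); 50% cap on the whole study population (5.5.1); 15 to 30 min added examination time (4.4), used here as a cautious stand-in for the delay.

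**Assumptions not in the protocol:** Tc-99m physical half-life 6 h; soft-tissue biological half-life h = 2 to 12 h; bone uptake stable; intrinsic SD of the paired log-ratio difference 0.10 to 0.20.

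**1. The time factor cancels.** For delay d in hours, f = 2^(d/6): 1.03 at 15 min, 1.06 at 30 min, 1.12 at 60 min. Decay divides both count rates by f and the longer acquisition multiplies both by f, so (B/f × f)/(S/f × f) = B/S. With B = 30 and S = 10 the ratio is 3.0 with or without the rule. Had the acquisition not been lengthened, (B/f)/(S/f) is also 3.0. The extra counts help the precision of the ratio, not its expected value.

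**2. Change in the later ratio.** With bone stable, the ratio is multiplied by 2^(d/h):

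| Delay | h = 12 h | h = 6 h | h = 4 h | h = 2 h |
|---|---|---|---|---|
| 15 min | 1.015 | 1.029 | 1.044 | 1.091 |
| 30 min | 1.029 | 1.060 | 1.091 | 1.189 |
| 60 min | 1.060 | 1.123 | 1.189 | 1.414 |

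The 60 min row is included because start-to-start delay can exceed the added examination time: it also depends on the length of the first session and the change of camera.

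**3. Shift in the group mean.** If a share q of patients is scanned in one order, the geometric-mean shift is the factor in step 2 raised to the power (2q − 1).
- One order only (q = 1): the whole shift, +2.9% to +18.9% at 30 min.
- Exactly 50/50: zero.
- Cap met over all 85 patients (43/42), with the 85 − 70 = 15 non-bone patients all on the smaller side: bone order is 43 against 42 − 15 = 27. Then 2q − 1 = 16/70 = 0.229, and the residual at 30 min is 1.0293^0.229 to 1.189^0.229, or about +0.7% to +4.0%.

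**4. Added variance under balance.** Each pair carries ±e on the log scale, with e = ln 2 × d/h. The variance of the paired difference is multiplied by (SD² + e²)/SD².
- 15-30 min and h = 2-12 h: e runs from 0.693 × 0.25/12 = 0.014 to 0.693 × 0.5/2 = 0.173. The multiplier runs from 1 + 0.014²/0.20² = 1.005 to 1 + 0.173²/0.10² = 4.0.
- 30-60 min and h = 2-6 h: e runs from 0.058 to 0.347, and the multiplier from 1.08 to about 13.

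The range is too wide for any single inflation figure to carry weight.

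**The case against.** The strongest reply is that the rule does the job it was written for. The primary criterion is a visual Likert score, restoring counts is useful there, and 5.5.1 never says that the rule corrects the ratio. The 50% cap further on in 5.5.1 also balances order, which takes most of the effect out of the mean. Both points stand, and they confine the finding to a secondary endpoint and, if both orders occur, mainly to precision. The cap is still incomplete: allocation follows appointment slots, and balance is set on all 85 patients.

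A second reply is that a covariate belongs in the statistical analysis plan, which is not to hand. That is fair for the model itself. But the protocol describes its rule as compensation for the delay, without limiting that to counts, and names its tests without a time or order term.

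A third is that three figures in section 5.5 are not reproduced and may give timings. So it cannot be said that decay scaling is the only measure in the plan, only that it is the only one in the visible text. Timings alone would still not correct a ratio.

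A reader might also infer that the 2-hour wait shows the plan relies on soft-tissue clearance. Section 2.2 gives the time and no reason, so the kinetics here are an assumption.

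**Conclusion.** The point holds for the sacroiliac/soft-tissue ratio. The cancellation is exact and needs no assumption: the stated compensation leaves any time-since-injection effect in the paired difference. Its size is illustrative and rests on the assumed delay, soft-tissue half-life and stable bone uptake: roughly 1.5-9% in the later ratio at 15 min and 3-19% at 30 min.

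If both camera orders occur, this is mainly avoidable variance, with a residual mean bias of about 0.7-4.0% in the 43/27 split at 30 min. If the standard Siemens scan is always first, the whole effect is confounded with the collimator. The two paragraphs of 5.5.1 can be read together if the standard examination may be done on either camera, but section 2.2 then disagrees. These sections must be reconciled.

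It is tempting to conclude that the primary comparison is biased, or that variance is inflated several-fold. The documents support neither: no effect on the Likert score can be quantified from them, and the inflation is set by inputs they do not give. Nor is a size claimed for the DaTSCAN ratio.

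**What to change.** - In 5.5.1, state that the longer acquisition compensates counts only, and reconcile the order statements in 5.5.1 and 2.2.
- In the bone patients, regress the paired log sacroiliac/soft-tissue ratio difference (LEHRS minus LEHR) on the signed difference in time since injection: D = α + β × (t_LEHRS − t_LEHR) + error. Take α, the difference at zero delay, as the device effect, and report the distribution of the delay beside it.
- For the DaTSCAN ratio, report the delay descriptively only. The 15 non-bone patients are shared among lung, thyroid, parathyroid and DaTSCAN examinations, so few pairs are expected.

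The cost is a sentence or two in the protocol and one covariate, with no new data or imaging, because section 5.6 already collects the injection and acquisition times. There are two drawbacks. A parametric paired model replaces the Wilcoxon test for this endpoint. And α is identifiable only if both orders occur, since otherwise zero delay lies outside the data. In that case the ratio comparison should be reported as confounded with time since injection.
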